### Trial design {8}

The study is a parallel two-group randomized controlled trial comparing the mood, cognitive performance, and brain activation of medical staff who undergo and do not undergo VR immersion after a night shift. In addition, data collected from a day shift are assessed and serve as a normal baseline. A total of 140 volunteers (including physicians and nurses) will be randomized in a 1:1 allocation to the intervention group and the control group by the block randomization method. fNIRS and abbreviated POMS assessments will be used at three time points collected throughout the study to assess how night shift and VR restorative environment immersion affect frontal cortex activity and mood in physicians and nurses [15, 16]. The collection time points are as follows: the first is collected during the day shift which is at least 3 days after the last night shift, and the last two are collected in the morning after the night shift (at 8:00–9:00 am) before and after VR intervention/rest. The interval between day shift and night shift assessments is at least 14 days. The intervention group will undergo immersion relaxation by watching their favorite VR restorative environment video for 10 min at 8:30 am after the night shift, while the control group will rest quietly for 10 min awake. The timeline design of the study is presented in Fig. 1.

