### Additional consent provisions for collection and use of participant data and biological specimens {26b}

On the consent form, participants are asked if their data can be used even if they choose to withdraw from the trial. Participants are also asked for permission of the research team to share relevant data with personnel from regulatory authorities, where relevant. The trial does not involve the collection of biological specimens.

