### Intervention description {11a}

The intervention time point is approximately 8:30 am after the night shift. All participants will complete the fNIRS and abbreviated POMS first, which takes approximately 20 min. Participants in the intervention group will recline comfortably on a sofa, wearing a VR glass loaded with an intelligent VR psychosomatic interactive training system (Ruixin, Ruihai Yinuo Intelligent Technology Co., Ltd., China) and watch 360° panoramic videos of the immersive VR natural restorative environment selected according to their preferences to relax themselves in the resting room. The intervention time will be 10 min. After the intervention, all participants will complete the fNIRS and abbreviated POMS again. Participants in the control group also recline comfortably on a sofa but only rest for 10 min without VR immersion. After relaxation, all participants will complete the fNIRS and abbreviated POMS again.

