### Criteria for discontinuing or modifying allocated interventions {11b}

Participants may quit at any time due to various reasons including failure to meet inclusion criteria or inability to continue VR intervention.

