### Outcomes {12}

The primary outcomes are the oxy-Hb and deoxy-Hb concentration of brain cortex acquired by fNIRS and VFT performances at three assessment time points (baseline, after the night shift before VR immersion, after VR immersion), to evaluate the alterations of in regional brain activity and functional brain network connectivity in the PFC. The secondary outcomes will be the abbreviated POMS scores at all the recorded time points.

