## Statistical methods

### Statistical methods for primary and secondary outcomes {20a}

Data analysis will start after all recruited participants have completed their assessments. To avoid bias, the data analyst will be blinded to the data. Participants who successfully complete the study according to the intervention plan will be included in the analysis. Missing data or any data collected that does not adhere to the protocol will be eliminated from data analysis.

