### Methods in analysis to handle protocol nonadherence and any statistical methods to handle missing data {20c}

Missing data and any data collected that does not adhere to the protocols will be removed from data analysis.

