### Adverse event reporting and harms {22}

It has been reported that a few people may experience physical discomfort, such as dizziness, when wearing VR glasses. Therefore, the trial can be stopped at any time if participants feel discomfort during the VR immersion, and the participants will be treated accordingly. The fNIRS system poses very little risk. Should an unforeseen serious adverse event occur, a case report will be written, and the trial manager will be notified within 24 h. All these events will be recorded and shared with the steering committee, ethics committee, and trial participants within the next 48 h. Participants will have the right to quit at any time for any reason during the trial.

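### As worded, the analysis rule drops VR participants who end the 10-minute session early, a discomfort-driven exclusion that can arise only in the VR arm

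*Protocol article*

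**What the plan says.** All references are to the protocol article.

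- **Analysis set, {20a}:** "Participants who successfully complete the study according to the intervention plan will be included in the analysis". The same paragraph eliminates missing data and collected data that depart from the protocol.
- **Non-adherence and missing data, {20c}:** "Missing data and any data collected that does not adhere to the protocols will be removed from data analysis".
- **Intervention plan, {11a}:** "The intervention time will be 10 min". The section also has all participants reassessed afterwards.
- **Discontinuation, {11b}:** "Participants may quit at any time due to various reasons including failure to meet inclusion criteria or inability to continue VR intervention".
- **Harms, {22}:** "It has been reported that a few people may experience physical discomfort, such as dizziness, when wearing VR glasses". The section then allows stopping for discomfort during immersion.
- **Control condition, {8}:** participants watch VR in one arm, "while the control group will rest quietly for 10 min awake" in the other.
- **Consent, {26b}:** "participants are asked if their data can be used even if they choose to withdraw from the trial".
- **Outcomes, {12}:** "The primary outcomes are the oxy-Hb and deoxy-Hb concentration of brain cortex acquired by fNIRS and VFT performances at three assessment time points". The abbreviated POMS is secondary.

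No as-randomised analysis and no sensitivity analysis to the completer rule appears anywhere in the article.

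**The concern.** T3 is the only assessment after the intervention, so the randomised comparison of VR with rest depends on it. Under the stated rule, whether a VR participant contributes to that comparison depends on whether they tolerated VR for the full time. That is a post-randomisation event, it depends on the allocated arm, and it is plausibly related to how the person feels at T3.

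On POMS and on the number of correct words, removing people who felt unwell would probably flatter VR. For the oxy-Hb and deoxy-Hb contrasts nothing in the document shows which way dizziness would move the signal, so the direction there is open.

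The Objectives {7} say that a positive result could lead hospitals to adopt VR for staff in every department. That decision concerns everyone who would be offered the headset, not only those who tolerate it for 10 minutes.

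**Working it through.** **Step 1: does the rule reach early stoppers?**

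- The intervention plan is 10 minutes of VR ({11a}).
- Only those who complete according to that plan are analysed ({20a}).
- Data that were collected but do not adhere are also removed ({20a}, {20c}), so the rule covers measured outcomes as well as absent ones.
- Early stopping for discomfort is foreseen ({11b}, {22}).

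A person who removes the headset partway has not completed the plan. No single sentence says so, but this is the natural reading of the sections together. The consent item in {26b} concerns permission to use data and does not alter the analysis rule.

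**Step 2: is the route one-sided?**

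Yes for VR discomfort, since controls wear no headset. Controls can be excluded for other reasons, such as not staying awake. Those reasons differ, so there is no basis for assuming that the two sets of exclusions cancel.

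**Step 3: the plan's own figure.**

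With d = 0.5, two-sided 5% and 80% power, the normal-approximation formula gives n = 2(1.960 + 0.842)²/0.5² = 62.8, so 63 per group. Then 63/0.9 = 70 per group, or 140 in total. The stated sample size {14} reproduces. Its 10% allowance protects power and does nothing about selection.

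**Step 4: how large could the bias be?**

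The document gives no stopping rate. It speaks only of a few people with discomfort, and discomfort is not the same as stopping. Assumptions:

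- k = 2, 4 or 7 of 70 VR participants stop and are excluded. Seven uses the whole 10% allowance on VR discomfort.
- Stoppers' mean POMS or word count is δ = 0.5 or 1 SD worse than that of other VR participants.
- There is no difference between arms when all randomised are counted.

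If the overall VR mean is zero and the retained mean is m, then m − (k/70)δ = 0, so the bias is m = (k/70)δ. The noncentrality is m / √(1/(70−k) + 1/70), with 138 − k degrees of freedom.

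| k | δ (SD) | Bias (SD) | Noncentrality | Two-sided rejection | Part favouring VR (nominal 2.5%) |
|---|---|---|---|---|---|
| 2 | 0.5 | 0.014 | 0.084 | 5.1% | 3.0% |
| 2 | 1.0 | 0.029 | 0.168 | 5.3% | 3.7% |
| 4 | 0.5 | 0.029 | 0.167 | 5.3% | 3.6% |
| 4 | 1.0 | 0.057 | 0.333 | 6.3% | 5.2% |
| 7 | 0.5 | 0.050 | 0.288 | 5.9% | 4.7% |
| 7 | 1.0 | 0.100 | 0.576 | 8.8% | 8.3% |

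Relative to the planned d = 0.5, the bias runs from 0.014/0.5 = 3% to 0.10/0.5 = 20%. If stoppers differ in the opposite direction, which is possible for the haemoglobin contrasts, the totals are the same but rejections favouring VR fall to between 2.0% and 0.6%.

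**Step 5: simulation check.**

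This used 200,000 runs per case, with the number of stoppers varying binomially and no effect among all randomised.

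| Stopping rate, δ | Stoppers excluded | All 70 analysed | Half of stoppers lack T3 (remaining bias) |
|---|---|---|---|
| 2/70, 0.5 SD | 5.1% | 5.0% | 5.0% (0.007 SD) |
| 4/70, 1 SD | 6.3% | 5.0% | 5.3% (0.028 SD) |
| 10%, 1 SD | 8.9% | 5.0% | 5.9% (0.048 SD) |

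**The case against.** **The exclusion is inferred.** No minimum exposure is defined, and {11b} and {22} speak of quitting or stopping the trial. Someone too dizzy to continue may simply leave without T3. That would be missing data, which a change to the analysis rule alone cannot recover. This stands as a limit. But {11b} is permissive, {22} may mean only the session, and {11a} has everyone reassessed, so T3 may well exist and the rule would then discard it. Where T3 would be lost, the protocol wording is what needs changing.

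**The direction is unknown for the haemoglobin outcomes.** This stands. The expected bias towards VR is confined to POMS (secondary) and word count (listed as primary in {12}).

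**The size rests on assumptions and is mostly small.** This also stands. The exposure is one 10-minute reclined viewing of self-chosen videos, in staff aged 20 to 45 with no history of neurological disease. The 8.8% case should carry little weight.

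**The error rates depend on the question asked.** If dizziness caused by VR produces the deficit, then no effect among all randomised implies a benefit among those who tolerate VR, and the extra rejections detect that benefit. They are pure selection error only if stoppers would have scored worse after rest too. This is correct, and the table refers to the effect among all randomised. That is still the effect relevant to adoption, and a completer subset of one arm set against all controls does not estimate the effect in tolerators without bias.

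**The trial is partly mechanistic and calls itself preliminary.** The Discussion puts weight on the neural mechanism and asks for a larger multicentre study. A completer analysis has a place for that aim, but both the Objectives and the Discussion also state an adoption aim, so it should not be the only analysis.

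**Conclusion.** The concern holds. The protocol states a completer rule and applies it to all outcomes. Read with the fixed 10-minute session and the anticipated discomfort, it removes early VR stoppers after randomisation by a route that controls cannot share. Blinding the analyst does not help, because the rule itself does the selecting.

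The consequence is probably modest: negligible with two stoppers, and of some concern only if stopping is common and stoppers are clearly worse off. The range depends entirely on the assumed stopping rate and deficit. This is a change that should be made because it is cheap and corrects a stated rule. It is not a flaw that invalidates the design. Confidence is medium.

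**What to change.** **Analysis sections {20a} and {20c}.** Analyse all randomised participants with T3 data in their assigned arm. State that a shortened VR session is not a reason to remove data. Keep the analysis of those who completed 10 minutes as supplementary.

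**Discontinuation {11b} and harms {22}.** State that ending the VR session early is not withdrawal from the trial. Offer T3 at the scheduled 08:40, at minimum the POMS, if the participant is willing and well enough. Record the minutes completed and the reason for stopping, which also gives hospitals tolerability data.

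**Cost.** This needs one change to the analysis rule and short protocol and consent wording. The planned sample size is unchanged and no extra visit is needed, because the participant, staff and equipment are already on site. Retaining participants also helps precision: t-test power at d = 0.5 is 83.6% with 70 per arm against 79.5% with 63.

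**Downside.** The most unwell stoppers may still decline T3 or give poorer recordings, so the bias is reduced and not removed (about half remains if half still lack T3). The estimated VR effect may also be slightly smaller.

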#### VFT performances and abbreviated POMS assessments

The VFT performances as well as neuropsychological measurements collected from the two groups will be compared using *t* tests.

#### fNIRS data

The raw fNIRS data will be bandpass filtered first and further processed to remove noise and drift. Neuroactivity in various regions of interest will be analyzed by constructing a general linear model for each subject then estimating parameters and obtaining contrast values of the oxy-Hb and deoxy-Hb signals. The contrast values will be averaged within groups and a group analysis will be performed using a *t* test. The averaged signal levels between two groups and between different assessment time points will be compared to determine the intervention effect.

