### Sample size {14}

In this protocol, a total of 140 participants (70 participants in two groups) will be recruited over an 18-month period. We aim to recruit an even distribution of age and gender to maximize statistical significance. The primary outcomes are the oxy-Hb and deoxy-Hb concentrations of the brain cortex acquired by fNIRS at baseline, after the night shift before VR immersion, and after VR immersion (or after rest). We assumed that the VR intervention group would show better recovery of PFC function than the non-intervention group. Because there are no pilot studies or previous studies, the sample size was calculated using G*Power software (downloadable from: https://download.cnet.com/G-Power/3000-2054_4-10647044.html), with 80% power, 2-sided 5% significance level, and a moderate effect size *d*=0.5. We assume that the mean of the two groups are the same. This sample size of 140 participants also allows for 10% loss to follow-up. Durán-Gómez N et al.’s study was used to estimate the baseline averages of oxy-Hb changes[7]. However, there are notable inherent differences between this protocol and Durán-Gómez N et al.’s study because the latter only described oxy-Hb changes before and after a night shift without other intervention [7].

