### Concealment mechanism {16b}

Once the consent form is received, a computer-generated random number from 1 to 140 will be assigned to that participant. Each number from 1 to 140 will be assigned a random group type: VR intervention or control. For the numbers randomly allotted for participants, the computer-generated random number assignment will be set such that it results in a 1:1 ratio, stratified by gender. The participant’s number will become the identifier for the participant’s collected data for data analysis. Once all participants have been enrolled and assigned, the list of which participants were distributed among the groups will be kept in an opaque, sealed envelope. Upon completion of consent, randomization, and baseline data collection, the participant will receive an opaque and sealed envelope associated with their randomized number. The researchers responsible for data collection and the analysis of outcomes will be blinded until after the completion of data analysis.

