### Methods for additional analyses {20b}

Further statistical analysis may be explored to account for interacting factors including gender, age, and different hours of sleep during the night shift.

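### The between-arm t tests are not adjusted for the pre-intervention value or the gender stratum, and the plan does not say which outcome contrast they compare; the cost is precision, not validity

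*Protocol article*

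**What the plan says.** The section on fNIRS data fits a general linear model within each subject and then states: "The contrast values will be averaged within groups and a group analysis will be performed using a" *t* test. Its last sentence adds that signal levels will be compared between groups and between time points to establish the intervention effect. For the other outcomes the article says: "The VFT performances as well as neuropsychological measurements collected from the two groups will be compared using" *t* tests, with no mention of time points.

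Three other places bear on this:

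- Plans for assessment and collection of outcomes {18a} has every participant measured at T1 (day-work baseline), T2 (08:10, before VR or rest) and T3 (08:40, after it).
- Concealment mechanism {16b} says that "the computer-generated random number assignment will be set such that it results in a 1:1 ratio, stratified by gender".
- Gender returns only in section {20b}, on additional analyses, where the article says: "Further statistical analysis may be explored to account for interacting factors including gender, age, and different hours of sleep during the night shift".

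Explanation for the choice of comparators {6b} also speaks of comparing outcomes before and after VR and after simple rest, without naming a model.

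**The concern.** T2 is the same measurement on the same person, 30 minutes before the outcome. If T2 and T3 are correlated, some of the between-person spread in T3 is already known before the intervention, and a T3-only *t* test leaves that spread in its error term. Gender is built into the randomisation, but it enters the analysis only as an optional exploration.

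The open choice of contrast matters too. A T3 comparison, a change-score comparison and a pair of within-arm before/after tests can give different answers from the same data, and the last of these does not estimate a between-arm effect at all. The article itself fixes the test as a *t* test, so this is not just a detail left to a fuller analysis plan. At stake are the power of a trial that calls its own sample small, and the freedom to choose the contrast after the data are seen.

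**Working it through.** **Inputs from the documents** (Sample size {14}): "with 80% power, 2-sided 5% significance level", d = 0.5, 70 per arm, 10% loss.

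**Assumptions.** The article gives no T2–T3 correlation r, so r = 0.3, 0.5 and 0.7 are used as a range. The SD is taken as equal at T2 and T3 and set to 1. Gender differences of 0.2, 0.5 and 1.0 SD, with equal numbers of men and women, are also assumed.

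**1. The plan's own figure.** For an unadjusted two-group comparison, n per arm = 2(1.960 + 0.842)² / 0.5² = 62.8, so 63. Allowing for loss, 63 / 0.9 = 70 per arm, or 140 in total. The stated number reproduces exactly and takes no credit for T2 or gender.

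**2. Power with 63 analysed per arm** (noncentral *t*, 124 degrees of freedom, noncentrality = effective d × √(63/2)). The effective d is 0.5 divided by the square root of the variance factor:

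- T3 alone: factor 1
- T3−T2 change: factor 2(1 − r)
- ANCOVA on T2: factor 1 − r²

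| r | T3 *t* test | Change: factor | Change: power | ANCOVA: factor | ANCOVA: power |
|---|---|---|---|---|---|
| 0.3 | 79.5% | 1.40 | 65% | 0.91 | 83% |
| 0.5 | 79.5% | 1.00 | 79.5% | 0.75 | 89.5% |
| 0.7 | 79.5% | 0.60 | 95% | 0.51 | 97% |

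The normal approximation behind the 140 gives 80.1% instead of 79.5% for the T3 test, which is immaterial.

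The ordering does not depend on the chosen r. Since 1 − r² ≤ 1, ANCOVA is never less precise than T3 alone. Since (1 − r²) / [2(1 − r)] = (1 + r)/2 ≤ 1, it is never less precise than the change score. Both statements ignore the one degree of freedom spent on the covariate, which is negligible here.

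**3. Gender, if the test is on T3 alone.** Let men and women differ by g SD, with proportion p women balanced across arms by stratification. The true variance of the arm difference reflects only within-gender variance (1), but the pooled variance in the *t* test is about 1 + g²p(1 − p). The real type I error is therefore about 2[1 − Φ(1.96 √(1 + g²p(1 − p)))]. With p = 0.5:

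- g = 0.2: √1.01 = 1.005, threshold 1.970, error 4.9%
- g = 0.5: √1.0625 = 1.031, threshold 2.020, error 4.3% (simulation about 4.2%)
- g = 1.0: √1.25 = 1.118, threshold 2.191, error 2.8% (simulation about 2.9%)

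**4. Gender, if the test is on change.** A gender difference of the same size at T2 and T3 cancels from T3−T2. In 20,000 simulated null trials with g = 1.0 SD, r = 0.6 and half women in each arm, type I error was 3.0% for the T3 test and 4.9% for the change test.

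**The case against.** The strongest reply is that the plan is coherent as it stands. The sample size is that of an unadjusted comparison, so the named test and the planned number match. Randomisation makes the unadjusted test unbiased, and chance imbalance at T2 is already covered by its standard error. This is also a condensed article, and covariate lists often sit in a fuller plan. All of that stands except the last step: the article does not leave the test open, it names it.

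A reader might infer that the analysis ignores every earlier measurement. The documents do not support that for fNIRS, because the last sentence of the fNIRS section and section {6b} plan comparisons between time points. T3-only is one possible reading. If the test is on change, T2 is used, and at r = 0.7 the shortfall against ANCOVA is only about 2 points of power. What those sentences do not supply is a single between-arm model. The VFT and POMS paragraph does not mention time points at all.

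A reader might also infer that leaving out gender invalidates the *p*-value. The error runs only in the conservative direction, is negligible at a 0.2 SD gender difference, and disappears for a change score when the gender difference is constant over time.

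One caution about the remedy stands. The design is open label, and section {16b} has participants receive their envelope after baseline collection, while the day and night assessments are at least 14 days apart. If the envelope were opened before T2, self-reported mood at T2 could reflect the known allocation. The article does not say when it is opened.

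**Conclusion.** The point holds as a matter of precision and of an undefined contrast. The article names plain *t* tests for the between-arm comparisons, states no adjustment for T2 or gender, and does not say which quantity is compared. ANCOVA is at least as precise as either valid reading. Against a T3-only test it gains about 4, 10 and 18 points of power at r = 0.3, 0.5 and 0.7; against a change score, about 18, 10 and 2 points. These sizes rest on assumed correlations and equal SDs at T2 and T3; the direction does not rest on the value of r.

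The documents do not support saying that the planned test is biased, that it inflates false positives, or that 140 is wrong. The gender effect on the error rate is conditional: it needs a T3-only test and a prognostic gender difference.

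**What to change.** In the two statistical paragraphs (VFT and POMS; fNIRS data), state one between-arm analysis: an ANCOVA, or an equivalent mixed model, of the T3 outcome on arm, T2 value and gender, reporting the adjusted difference with a 95% confidence interval. Apply it to the fNIRS contrast, the VFT word count and the POMS total score. T1 may be added as a further covariate; no gain from it has been calculated here. Label the before/after comparisons within arms as descriptive. Keep gender in section {20b} only for interaction analyses.

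State in section {16b} that T2 is completed before the participant learns the allocation.

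The cost is wording, plus control over when the envelope is opened. No extra participants, visits or measurements are needed, and the sample size can stay at 140. The change should be made before any outcome data are analysed.
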